As mentioned above, component studies are an important tool for examining how therapies work, and they provide an appropriate way to identify the active elements of interventions [48]. With this study design, multicomponent treatments are decomposed, and the complete intervention is compared to an intervention in which a component is eliminated (dismantling studies) or to an intervention with an addition component (additive studies; [49]). There are few studies with a dismantling design in interventions for depression [50]. A recent comprehensive systematic review and meta-analysis of dismantling studies of psychotherapies for adult depression included only 16 studies, none with an Internet-based intervention [15].

Our research group has developed an Internet-based cognitive-behavioral treatment protocol that also includes PPs for patients suffering from depressive symptoms. It has shown its efficacy in different RCTs [51–53]. The results show that this intervention is effective overall, but we do not know the specific contribution of each of its therapeutic components. Using a dismantling strategy could help to identify the contribution of BA and PPs (its main therapeutic components) to the therapeutic change. As a result, this information can contribute to improving intervention programs for depression.

To the best of our knowledge no study with a dismantling design exists with an Internet-based treatment protocol for depression, and even less so with the specific objective of discovering the contribution of BA and PPs.

The objectives of the current study are to (a) evaluate the efficacy at post-treatment and follow-ups (3, 6, and 12 months) of a complete Internet-based protocol for depressive symptoms (including motivation, cognitive restructuring, BA, PPs, Relapse prevention), a protocol for depressive symptoms without PPs, and a protocol for depressive symptoms without a BA component, all of them administered through the Internet to patients with mild to moderate depressive symptoms; (b) analyze the mediators of change in depressive symptoms; and (c) study the acceptability and usability of the intervention.

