##### Acceptance, satisfaction and usability outcomes

Expectation of treatment scale and opinion of treatment scale these two scales are adapted from Borkovec and Nau [78]. Each scale contains 5 items, regarding whether the treatment is logical, treatment satisfaction, the treatment’s utility for other psychological problems, and the treatment’s usefulness for the patient’s specific problem. The expectation scale is administered at the post-module 2 assessment, when the treatment has been explained to the participants, and the opinion scale is administered at the end of the treatment, with the aim of assessing satisfaction. Our group has used this questionnaire in several research studies [51, 79].

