**System Usability Scale (SUS)**

The SUS [80] is a brief, reliable scale for measuring the usability of a program. It consists of a 10-item questionnaire with 5 response options, from 0 (“strongly disagree”) to 4 (“strongly agree”). Its purpose is to collect the user’s opinion about the usability of the system, and unacceptable usability may indicate that the user has had technical difficulties with the program. The SUS adjective rating scale (from “Worst imaginable” to “Best imaginable”) will be used to provide a qualitative comparison of usability scores [81].

The study measures and area and time of assessment are summarized in Table 4.

**Table 4 Tab4:** Study measures, assessment area and time of assessment

Outcomes	Concept	Instrument	Time of assessment			
			BL	Post-T	Post-M	FUPs (3, 6, 12)
Diagnostic interview	Diagnosis	MINI Neuropsychiatric Interview	X	X		X
Primary	Depression	BDI-II	X	X		X
	Positive and Negative affect	PANAS	X	X	X	X
Secondary	Resilience	CD-RISC	X	X		X
	Depression	ODSIS	X	X	X	X
	Perceived Stress	PSS	X	X		X
	Anxiety	OASIS	X	X	X	X
	Quality of life	QLI	X	X		X
	- Well-being	PHI	X	X		X
	- Anticipatory pleasure	EOS	X	X		X
	- Environmental reward	EROS	X	X		X
	Acceptance, satisfaction and usability outcomes					
	- Expectation of treatment	Expectation of Treatment Scale	X			
	- Opinion of treatment	Opinion of Treatment Scale		X		
	- Usability	SUS		X		

Note: *BL* Baseline, *Post-T* Post-treatment, *Post-M Post Module*, *FUPs (3,6,12)* 3, 6, and 12-month follow-ups, *BDI-II* Beck Depression Inventory-II, *CD-RISC* Connor-Davidson Resilience Scale, *PANAS* Positive and Negative Affect Scale, *ODSIS* Overall Depression Severity and Impairment Scale, *PSS* Perceived Stress Scale, *OASIS* Overall Anxiety Severity and Impairment Scale, *QLI* Quality of Life Index, *PHI* Pemberton Happiness Index, *EOS* Enjoyment Orientation Scale, *EROS* Environmental Reward Observation Scale, *SUS* System Usability Scale

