**Sample size and power calculations**

The a priori sample size determination was performed based on the main objective of this investigation. Following Cohen’s (1988) guidelines, we assumed a proportion of explained variance of low magnitude for the interaction between the type of intervention and the measurement occasion, that is, 0.01. For a significance level of 5%, statistical power of 80%, assumed sphericity, and correlation of .7 between repeated measures (following Rosenthal’s 1991 recommendation), the total sample size needed was 147 participants (49 per intervention group). To this figure, an additional 30% was added to anticipate potential dropouts. Therefore, the total sample size of the study was 192 participants (64 per intervention group). Sample size calculations were carried out with the statistical program G*Power 3.1.9.2 [82].

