For acceptability and usability measures, data analysis will be based on completers. Separate multivariate analysis of variance (MANOVA) for expectations, satisfaction, and usability will be performed, where all items are entered into the MANOVA as dependent variables, and the experimental group as a fixed factor (independent variable).

Finally, multiple regression analysis and mediation analysis will be conducted to explore potential predictors and mediators of depressive symptoms. Mediation analyses will be performed through bootstrap regression analysis using the Preacher and Hayes (2004) approach. All statistical analyses will be conducted using IBM SPSS Statistics for Windows, version 23.

We will review the state of the art analytical methodology for RCT before performing the analyses of the data, in order to use the best statistical analysis procedure. Thus, there may be some variations in the statistical analysis procedures.

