In sum, this study has several strengths. To the best of our knowledge, this is the first randomized dismantling intervention study for depression with the aim of exploring the contribution of a PPs component and the BA component in an Internet-based intervention. The three protocols are online interventions, helping to reach many people who need psychological treatments and would not otherwise have access to them. Furthermore, acceptability and usability measures will be included in order to assess the intervention’s feasibility and acceptance, in addition to an efficacy study. Finally, potential mediator mechanisms will be explored to identify the variables that lead to changes in depressive symptoms.

We are aware that this study has limitations. One of them is that the number of BA and PPs modules in the *IBAc* and *IPPc* is higher than in the *IGc*, although the clinical content is the same in the global protocol and in the protocols for the BA and PPs components. The reason for this is that the three protocols contain the same total number of modules (8 modules per each) and a similar number of words. We give all the patients the same amount of time to do the intervention to try to control this. Another limitation is that the dropout rates are expected to be high (around 30%) [103]. Efforts will be made to minimize the dropout rates by providing ICT and human support. Approaches to handling missing data will be considered and assessed using sensitivity analyses in order to apply the most robust and adequate method, based on both the missing data patterns and recommendations found in the literature (i.e., [87, 88]. In addition, difficulties in the recruitment phase will be considered.

In summary, this study extends the current literature about Internet-based interventions for depression. If positive results are achieved, they may have an important impact by providing better knowledge about the core elements of evidence-based treatments for depression.

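### Acceptability and usability are to be analysed in undefined completers, which on the natural reading drops expectation scores already collected and conditions the arm comparison on staying in the programme

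*Protocol article*

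**What the plan says.** The third objective in the Background is to "study the acceptability and usability of the intervention". The Statistical analysis section gives the analysis set: "For acceptability and usability measures, data analysis will be based on completers". It then plans separate MANOVAs of the expectation, satisfaction and usability items with experimental group as the factor.

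The same section applies intention-to-treat to primary and secondary outcomes. It adds a per-protocol analysis for patients who finish every module, and concedes that this one carries selection bias. The acceptability analysis has neither an all-randomised companion nor that caveat.

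On collection, the Instruments section says: "The expectation scale is administered at the post-module 2 assessment, when the treatment has been explained to the participants". Table 4 has a row for the "Expectation of Treatment Scale" that is marked at baseline, with the post-module column left blank. The opinion scale and the SUS are marked only at post-treatment. According to the Interventions section, participants do that assessment once they have completed the eight modules. Under Support, the call asking for a qualitative opinion comes after the post-assessment.

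On dropout, the sample size section says that "an additional 30% was added to anticipate potential dropouts", and the Discussion expects a rate of about 30%.

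**The concern.** Whether someone stays in a self-paced online programme is plausibly related to how acceptable and usable they find it. Restricting the analysis to those who finish therefore selects on something close to the outcome, and does so after randomisation, so the comparison of arms loses the protection of random allocation. A protocol that drives away its dissatisfied users could look as acceptable as one that keeps them.

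For the expectation scale, the rule can also discard data the trial already holds. The conflict over when that scale is given adds a second problem. A score at baseline and a score after two modules are different quantities, and the choice also determines whose scores exist.

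At stake is the answer to objective (c), not the efficacy results.

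**Working it through.** **1. What completers could mean.** The acceptability paragraph does not define the word. Two places in the protocol point to finishing all eight modules: the per-protocol description in the Statistical analysis section, and the rule in the Interventions section that post-treatment follows the eighth module. The other possible reading is people who completed the questionnaire in question. The two readings have different consequences for each scale:

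| Scale | When given | If completers = finished eight modules | If completers = answered the scale |
|---|---|---|---|
| Expectation | after module 2 (text) or baseline (Table 4) | scores of later leavers dropped by rule | nothing dropped |
| Opinion, SUS | post-treatment, after module 8 | leavers have no score to drop | leavers have no score |

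The analysis rule matters mainly for expectation. For opinion and SUS the gap arises when the data are collected, and changing the analysis set alone would not recover them.

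**2. How the timing conflict interacts.** At the advised pace of one module every two weeks, the assessment after module 2 falls about 2 × 2 = 4 weeks into treatment. If the text is right, the scores at risk are those of people who stop during modules 3 to 8. If Table 4 is right, they are those of anyone who answered at baseline and later stopped.

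**3. The plan's own numbers.** The total of 192 reproduces from the stated 147: 147 × 1.30 = 191.1, rounded up to 64 per arm, and 3 × 64 = 192.

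**4. Size of the excluded group.** At 30% dropout, 0.30 × 192 = 57.6, about 58 people. That leaves 192 − 57.6 = 134.4, about 134, or 0.70 × 64 = 44.8 per arm. This is an upper figure for a 30% rate, because the protocol does not say how much dropout falls before post-treatment and how much during the 3, 6 and 12-month follow-ups.

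**5. Effect on a mean rating.** Let d be the proportion who leave before rating, and Δ the amount (in SD) by which leavers would rate lower than completers. The all-randomised mean is (1 − d)·μ + d·(μ − Δ) = μ − dΔ, where μ is the completer mean. The completer mean is therefore too high by dΔ. The documents do not give Δ, so the values below are assumptions:

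| d | Δ = 0.25 | Δ = 0.5 | Δ = 1.0 |
|---|---|---|---|
| 0.20 | 0.05 | 0.10 | 0.20 |
| 0.30 | 0.075 | 0.15 | 0.30 |
| 0.40 | 0.10 | 0.20 | 0.40 |

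**6. Effect on the contrast between two arms A and B.** The bias is d_A·Δ_A − d_B·Δ_B. With equal dropout and an equal gap it is zero. With a common Δ and dropout of 25% against 35% (assumed), it is 0.10 × Δ = 0.025, 0.05 or 0.10 SD. With 20% against 40% (also assumed), it is 0.20 × Δ = 0.05, 0.10 or 0.20 SD.

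**The case against.** The strongest reply is that the sentence can be read as covering those who completed the questionnaire, in which case no expectation score is lost. The per-protocol set has its own name elsewhere, which lends this some support. The reading cannot be excluded. What stands is that the term must be defined, because the natural reading from the rest of the article is the harmful one.

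A second reply is that an end-of-programme satisfaction score among people who used the whole programme is a legitimate quantity. That is true if it is reported as such. Objective (c) concerns the intervention without that restriction, and the Discussion promises the acceptability of each intervention.

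A third is that the arms have the same number of modules, similar word counts, the same time limit and the same support, so nothing in the protocol predicts unequal dropout. This is fair, and the between-arm bias is therefore conditional.

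A reader might also infer stronger claims that the document does not support:

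- **That ratings will be inflated in every arm.** This depends on leavers being less satisfied, which is plausible but not documented.
- **That 30% of participants are certain to be excluded.** The figure is a planning expectation with no time point attached.
- **That expectation is measured before most dropout occurs.** No dropout timing is given. The point needs only that some people stop after answering.
- **That the plan is deficient for not naming adherence as an acceptability outcome.** A condensed article that follows CONSORT and CONSORT-EHEALTH may leave this to the full protocol. Ranking adherence as the leading outcome would be a preference.

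Finally, the closing statement that analysis procedures may vary does not answer the point, since it names no other analysis set.

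**Conclusion.** The concern holds in a limited form. The protocol fixes a completer analysis for objective (c) without defining completers. If the term means all eight modules, that analysis discards expectation scores already in hand and compares the arms conditional on a post-randomisation event related to acceptability. For opinion and SUS, leavers are lost mainly because the scales are offered only after module 8.

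Up to about 58 of 192 people are affected if all the planned 30% dropout precedes post-treatment. The illustrative inflation of completer means is about 0.08 to 0.30 SD, for an assumed gap of 0.25 to 1.0 SD. There is no bias between arms unless dropout or the gap differs by arm.

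The conflict between the text and Table 4 on the expectation scale is a separate, definite inconsistency that needs no assumption. Severity is minor to moderate, since the primary outcomes, BDI-II and PANAS, are not touched.

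**What to change.** 1. Define completers in the acceptability paragraph, and label any rating restricted to them as applying to completers only.
2. Analyse expectation in all randomised participants who answered it, whether or not they finished.
3. Report modules completed and dropout by arm, in all randomised participants, alongside the ratings. Table 3 shows that the platform already displays progress and access days, so this needs tables but no new data.
4. Make the opinion scale and the SUS available at the end of the 16-week window to those who have not finished, and analyse everyone who responds.
5. Reconcile the Instruments text (after module 2) with Table 4 (baseline) on when expectation is measured.

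Items 1, 2, 3 and 5 cost wording and a few tables. Item 4 adds a small contact for people who stopped. Their response will be partial, so some selection will remain and the response rate by arm should be shown.

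### Usability is tested only by a MANOVA on the ten SUS items; a test of the SUS score would be a cheap, low-severity improvement

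*Protocol article*

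**What the plan says.** The Statistical analysis section states: "Separate multivariate analysis of variance (MANOVA) for expectations, satisfaction, and usability will be performed". In each, "all items are entered into the MANOVA as dependent variables, and the experimental group as a fixed factor". The analysis set is also fixed: "For acceptability and usability measures, data analysis will be based on completers".

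The instruments are described earlier. The SUS is a single scale for the usability of a program: "It consists of a 10-item questionnaire with 5 response options". Its adjective rating "will be used to provide a qualitative comparison of usability scores". No inferential test of a SUS score is named.

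For the expectation and opinion scales the text reads "Each scale contains 5 items, regarding whether the treatment is logical, treatment satisfaction". It goes on to utility for other problems and usefulness for the patient's own problem. No total or mean is defined for either scale.

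Tukey or Games-Howell follow-up and effect sizes with confidence intervals are described after the repeated-measures ANOVA of primary and secondary outcomes. The paragraph on the MANOVAs names no follow-up. The section ends by allowing that procedures may vary.

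**The concern.** The protocol uses a SUS score when it describes usability, but its only significance test for usability never compares that score. The test asks whether any linear combination of ten items differs between three arms. A reader would more naturally want to know whether one protocol is more usable overall, and by how much.

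If the arms differ in that general way, the item test spreads the same signal over ten times as many degrees of freedom as a test of the score. A real difference in overall usability could then go undetected. A significant result would show only that some combination of items differs, with no estimate on the scale that the adjective rating uses.

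**Working it through.** **Stated figures.** The protocol gives no power for the usability analysis, so there is no figure of its own to reproduce on this point. Its power statement ("For a significance level of 5%, statistical power of 80%, assumed sphericity, and correlation of .7 between repeated measures") concerns the interaction of intervention and occasion. That calculation gives 147 participants, and 147 × 1.3 = 191.1, which becomes 192 (64 per arm).

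**Inputs from the protocol**
- Arms: 3.
- Items: SUS 10; expectation 5; opinion 5.
- Completers: 192 × (1 − 0.30) = 134.4, about 45 per arm, so N = 135. The 30% dropout is in the sample size and Discussion sections.
- Alpha 0.05, stated for the main objective and assumed here.

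**Inputs assumed, because the protocol gives none**
- One arm differs from the other two by 0.5 SD (or 0.6 SD) of the total score.
- The shift is the same on every item.
- Items have equal variance and a common correlation r of 0.3 or 0.5.

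**Degrees of freedom.** Hypothesis df for the MANOVA = p × (3 − 1).
- SUS: 10 × 2 = 20.
- Each 5-item scale: 5 × 2 = 10.
- A single score: 2.

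For three groups Wilks' lambda has an exact F with 2p and 2(N − p − 2) df: 20 and 246 for the SUS, 10 and 256 for a 5-item scale.

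**Why the power differs.** Let each item shift by δ (item SD = 1).
- The total shifts by pδ and has variance p[1 + (p − 1)r]. Its squared standardised shift is d² = pδ² / [1 + (p − 1)r].
- The squared Mahalanobis distance for the p items is the same quantity, pδ² / [1 + (p − 1)r].

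So both tests see the same signal. The MANOVA spreads it over 20 or 10 df instead of 2. This is also why the result hardly depends on r.

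**Power of ANOVA on the score.** With one arm shifted, λ = n × d² × 2/3.
- d = 0.5: λ = 45 × 0.25 × 2/3 = 7.5; noncentral F with 2 and 132 df gives power 0.677.
- d = 0.6: λ = 45 × 0.36 × 2/3 = 10.8; power 0.837.

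**Power of the item MANOVA by simulation** (Wilks' lambda, 6000 runs per setting, r = 0.3 and 0.5; the ANOVA column is from the same runs)

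| Scale | Shift | MANOVA on items | ANOVA on score |
|---|---|---|---|
| SUS, 10 items | 0.5 SD | 26–28% | 67–68% |
| SUS, 10 items | 0.6 SD | 40% | 83–84% |
| 5 items | 0.5 SD | 38–39% | 68% |

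A second parametrisation, with arms at −d, 0 and +d and d set so that ANOVA on the score has 80% power, gives the MANOVA about 37% for 10 items and about 51% for 5 items. This holds for r from 0.3 to 0.7 at 45 per arm, and results are close at 49 and 64 per arm.

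**Type I error.** With no difference between arms, both tests reject in about 5% of runs (4.5% to 5.2%).

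**When the shift is not even.** Take the −d, 0, +d pattern with one quarter of the λ that gives ANOVA on the score 80% power, and the 10-item scale.
- Effect on 5 of 10 items: MANOVA 55% (r = 0.3) and 91% (r = 0.5), against 26% and 27% for ANOVA on the total.
- Effect on one item: MANOVA close to 100%, against 24% and 28%.

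The ranking reverses, so the loss applies only to a difference in general usability.

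**The case against.** The strongest reply has four parts.

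1. **The planned test is valid, and which test is better depends on an unknown effect pattern.** This stands. Type I error is held, and the MANOVA wins clearly when the effect is concentrated on some items. The case for the score is that the SUS is presented as a measure of usability as a whole, which makes a general difference the natural target.

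2. **A reader might infer that all three scales lose most of their power.** The documents do not support that. For a 5-item scale under an even shift, power falls from about 68% to about 38%, a loss of under half. The expectation and opinion items also differ in content and have no defined total, so a multivariate item test is defensible there.

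3. **A reader might infer that the MANOVA result has no usable direction.** That is too strong. Item means by arm would show direction, SUS scores are to be compared descriptively, and an omnibus three-arm ANOVA has no direction either. Follow-up after a MANOVA may also be set out in a fuller plan. The gain comes from estimated pairwise differences on the score.

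4. **A reader might infer that objective (c) asks whether the arms differ in usability.** It does not. It speaks of studying the acceptability and usability of the intervention, and no between-arm hypothesis is stated. Still, the protocol does plan a between-arm test with arm as the factor, so it is fair to ask whether that test suits the scale.

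The closing allowance for procedural changes makes an edit easy, but it does not replace the method named.

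**Conclusion.** The point holds in a narrow form, for the SUS. The only planned test of usability is an item MANOVA with 20 hypothesis df, while the score that the protocol uses descriptively is never tested. For a general difference of 0.5 SD, power is about 27% instead of 67% to 68%.

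This rests on about 45 completers per arm, one shifted arm, an even shift and equal item correlations of 0.3 to 0.5. Only the number of completers can be derived from the protocol. With effects on a subset of items the MANOVA can be the more powerful test.

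For the expectation and opinion scales the point is at most a suggestion. Severity is low: these are acceptability and usability measures, outside the primary analysis and the sample size, and no efficacy conclusion depends on them.

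**What to change.** In the Statistical analysis section, name the SUS total score as the main usability outcome, compare it by one-way ANOVA on arm, and report pairwise differences with 95% CIs. Keep the item results, as a descriptive table or as the planned MANOVA, as supporting.

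At 45 per arm the standard error of a pairwise difference is √(2/45) = 0.211 SD. An unadjusted 95% CI therefore extends about 1.98 × 0.211 = 0.42 SD either side.

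For the expectation and opinion scales a mean-score analysis is optional. If it is wanted, define the score first.

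The cost is about one sentence, with no extra data. The downside is that a difference confined to a few items is diluted in the total, which is the reason to keep the item results.
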